#### Micronutrients

##### Iodine status

Iodine is required for the synthesis of thyroid hormones, which are essential for human brain development, and iodine supplementation during pregnancy has been shown to mitigate the adverse effects of iodine deficiency.^22^ Using banked samples, we will test urinary iodine concentration at the Ethiopia Public Health Institute (Addis Ababa, Ethiopia) to determine the impact of ENAT’s intensive iodised salt intervention component during pregnancy on infant neurodevelopment and thyroid function. DBSs will also be tested for thyroid function markers (TSH, Free T4, Thyroglobulin) at the Human Nutrition Laboratory (Zurich, Switzerland). Of the samples being tested for urine iodine, a subset of 10% will be retested and we will calculate a coefficient of variation to determine any sample-to-sample variability.

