### Study design

The ENAT study was a pragmatic, open-label 2×2 factorial, randomised clinical effectiveness study with cluster-randomisation of an enhanced nutrition package (ENP) intervention and individual-level randomisation of an enhanced infection management package (EIMP) intervention (figure 1). The detailed study protocol has been previously published^11^ and this protocol paper details the protocols for biospecimen collection and planned analysis.

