### Study interventions

#### Enhanced Nutrition Package (ENP) Intervention

The ENP intervention consisted of (1) nutritional counselling, (2) monthly supply of high quality adequately iodised salt, (3) iron-folate (IFA) tablets and (4) women with an upper-middle arm circumference (MUAC) of <23 cm received a fortified balanced energy-protein (BEP) supplement monthly. The BEP supplement was a locally produced, micronutrient fortified, corn soya blend (World Food Programme Super Cereal). The nutrition routine care arm consisted of IFA provision.

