##### Study nutrition supplements

###### Iron-folate (IFA)

Following Ethiopian Ministry of Health recommendations, the health system distributes 60 mg iron plus 400 ug folic acid supplements to be taken once daily during pregnancy to all women. Due to our formative work indicating hesitancy to take such supplements in fear of delivering ‘big babies’ and gastric irritation as a side effect,^19^ intensive counselling was provided to pregnant women in the ENP arm to encourage compliance, as well as compliance monitoring and resupply at ANC visits as needed.

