###### Iodised salt

A regular monthly household supply of adequately iodised salt (Waff Manufacturing, 30–40 ppm potassium iodate, 600 g bottle) was provided to women in the ENP arm for household consumption, and they were encouraged to use approximately three pinches daily.

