###### Fortified Balanced-Energy Protein (BEP)

A regular monthly supply of locally produced, micronutrient fortified, corn soya flour blend (Super Cereal, Faffa Food Share Company, Addis Ababa, Ethiopia) was provided to women in the ENP arm with a MUAC<23 cm at enrolment or any ANC visit. The composition of the BEP used is described in table 1.

**Table 1 T1:** Super cereal corn soya blend composition (per daily 200 g serving)

Nutrient	Units	ENAT CSB content(200 gm)	Recommended target*
Energy	Kcal	760	250–500 Kcal per daily serving†
Protein	gm	28	14–18 g†
Fat	%	12	10%–60% of energy
Vitamin A	mcg RE	2076	550–770‡
Vitamin D	mcg	22.1	10–15
Vitamin E	mg	16.6	16–19
Vitamin K	mcg	60	72–90
Vitamin B_1_	mg	0.4	1.2–1.4
Vitamin B_2_	mg	2.8	1.3–1.6
Vitamin B_3_	mg	16	14–18
Folic acid	mcg	220	400–600
Vitamin B_6_	mg	2.0	1.7–2.0
Vitamin C	mg	180	100–120
Calcium	mg	724	500–1500
Iron	mg	8	22–27
Iodine	mcg	80	209–290
Phosphorous	mg	560	300–700
Zinc	mg	10	15–20

* Targets are results of an Expert Consultation held at Bill and Melinda Gates Foundation.

† Energy balance from macronutrient: portion size can be doubled in settings of high energy gaps, such as maternal malnutrition and where prevalence of birthweightbirth weight is high.

‡ Macronutrient recommendations were primarily based uponon Institute of Medicine () estimated average requirements () and recommended dietary allowances () values.

CSB, corn soya blend; ENAT, Enhancing Nutrition and Antenatal Infection Treatment.

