### Gut enteropathogens

It has been hypothesised that enteropathogen infection may cause intestinal inflammation and contribute to stunting and micronutrient deficiencies in infants.^13^ Stool samples collected in DNA/RNA shield will be sent to the University of Virginia for testing using custom-designed TaqMan array cards (TAC). We will determine the pathogenic burden within pregnant women. We will also examine the impact of the ENAT deworming interventions on stool pathogens.

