#### Intervention effects

In our primary analysis, we will examine differences in biomarkers or ’omics profiles across the randomised intervention study arms. We will use intention-to-treat as the primary analyses where individuals are analysed according to their originally assigned study arm, and in secondary analysis, we will also explore effects of individual interventions (ie, BEP) and adherence/dose. Outcomes will be compared between the primary factors (ENP or EIMP) to determine their marginal effects (ENP vs not-ENP, and EIMP vs not-EIMP). We will estimate differences in biomarkers, using linear mixed regression models. Potential confounding bias should be minimised due to the randomised study design; however, we will assess group differences in demographic and clinical characteristics at both cluster- and individual randomisation levels, as recommended by Consolidated Standards of Reporting Trials.^28^ Baseline covariate imbalances associated with both the outcome and exposure status (p<0.10) will be included in adjusted models as potential confounders. Multiple births will be excluded from analyses using birth outcomes due to the known increased rate of preterm birth and growth restriction among multiple deliveries. When large volumes of tests are conducted for metabolomics or genomics analyses, we will use the Benjamini-Hochberg method to correct for multiple testing, as appropriate.

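### Effects are attributed to iodised salt and deworming, but only the ENP and EIMP packages were randomised; the exploratory BEP and adherence analyses also need a comparison made by assignment or an observational label

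*Protocol article*

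**What the plan says.** Study design describes "cluster-randomisation of an enhanced nutrition package (ENP) intervention and individual-level randomisation of an enhanced infection management package (EIMP) intervention". No single component is allocated separately.

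**Nutrition package.** "The ENP intervention consisted of (1) nutritional counselling, (2) monthly supply of high quality adequately iodised salt, (3) iron-folate (IFA) tablets", with BEP added for women whose MUAC is below 23 cm. The BEP subsection says the supplement "was provided to women in the ENP arm with a MUAC<23 cm at enrolment or any ANC visit". Routine care also provides iron-folic acid (IFA), but the IFA subsection adds that "intensive counselling was provided to pregnant women in the ENP arm to encourage compliance", with compliance monitoring and resupply.

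**Infection package.** EIMP combines screening and treatment of urinary, sexually transmitted and reproductive tract infections with enhanced deworming.

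**Aims stated for single components.**
- Iodine status: the effect of the "intensive iodised salt intervention component during pregnancy on infant neurodevelopment and thyroid function".
- Gut enteropathogens: "We will also examine the impact of the ENAT deworming interventions on stool pathogens".
- Intervention effects, as secondary analysis: "we will also explore effects of individual interventions (ie, BEP) and adherence/dose".

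The primary contrasts under Intervention effects are ENP against not-ENP and EIMP against not-EIMP, by intention to treat.

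**The concern.** The unit of attribution in the stated aims is smaller than the unit of randomisation. A difference in thyroid function or neurodevelopment between ENP and routine care could come from salt, counselling, better IFA adherence, BEP or any mixture of these. If it is reported as an iodised-salt effect, the trial claims evidence that it does not hold. The same applies to deworming within EIMP.

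BEP raises a different problem. It was given according to nutritional status, so an analysis by receipt or dose is not a comparison of randomised groups. The effect of nutrition interventions, BEP included, on multiomics profiles is the stated consortium interest in the Introduction, so readers are likely to rely on any BEP result.

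**Working it through.** The article gives no effect size, power or sample size for these component questions, so there is no figure of its own to reproduce. The check is whether the effects can be identified.

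**1. Can the components be separated?** Take the eight cells formed by ENP (0/1), EIMP (0/1) and MUAC below 23 cm (0/1), and give each component its own column:

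| Column | Value in a cell |
|---|---|
| Intercept | 1 |
| Low MUAC | low |
| Counselling | ENP |
| Iodised salt | ENP |
| IFA support | ENP |
| BEP | ENP × low |
| UTI/STI/RTI screening-treatment | EIMP |
| Presumptive deworming | EIMP |
| Stool screening-treatment | EIMP |

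There are nine columns, but only five are distinct: 1, low, ENP, ENP × low and EIMP. The rank is 5. Salt, counselling and IFA support are one and the same column, and so are the three EIMP components. No model fitted to these groups can separate salt from the rest of ENP, or deworming from the rest of EIMP.

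**2. Does an iodine measure make the salt claim specific?** Not in BEP recipients. Table 1 gives 80 mcg iodine per daily 200 g serving and a target of 209–290 mcg:
- 80/290 = 0.28
- 80/209 = 0.38

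A full BEP serving therefore supplies 28% to 38% of the target, in addition to the salt. The salt is described only as "30–40 ppm potassium iodate, 600 g bottle" for the household, with use suggested in pinches. The split of iodine intake between salt and BEP cannot be worked out from the article without assuming a salt intake.

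**3. What can be learned about BEP?** BEP does have its own column, ENP × low MUAC. Write R for the combined effect of the other ENP components, B for the BEP effect, and λ for the share of ENP women at or above 23 cm at enrolment who later qualified for BEP. With B taken as the same in both strata:
- ENP v not-ENP, enrolment MUAC below 23 cm: R_low + B
- ENP v not-ENP, enrolment MUAC 23 cm or above: R_high + λB
- Difference (the interaction): (R_low − R_high) + (1 − λ)B

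The first line is the package including BEP, not BEP. The interaction is attributable to BEP alone only if R_low = R_high, and even then it is diluted by λ. The article does not report λ.

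**4. What would receipt or dose comparisons do?** Within ENP, every woman below 23 cm at enrolment was due BEP, so that stratum has no comparator that was not offered it. Recipients and non-recipients differ in nutritional status by the rule itself. Women who first qualify at a later antenatal visit are classified by a measurement taken after randomisation. Adherence and dose are self-selected. The confounding provision under Intervention effects (randomisation, plus covariates selected at p<0.10) does not deal with allocation by MUAC.

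**The case against.** The strongest reply is that the only contrasts actually specified are the package-level ones. The iodine and enteropathogen sentences sit under Planned laboratory analyses and explain why assays are run. Read with Intervention effects, they would be analysed as ENP v not-ENP and EIMP v not-EIMP, which are valid. That stands as regards the analysis. It does not rescue the wording: the Iodine status sentence names the salt component as the cause, whereas the sections on inflammation and iron status refer to the ENAT interventions in general. An unseen analysis plan could define an estimator, but it could not make the design separate salt from its co-interventions.

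Three stronger readings are tempting but unsupported:
- *That the primary results are confounded.* They are not. For salt and deworming the fault is bundling, which affects attribution.
- *That the plan compares BEP recipients with non-recipients, so undernutrition will be read as a BEP effect.* No such comparison is written. The BEP analysis is secondary and exploratory with no comparator named, and an article may leave that to the full plan. Nor can a bias be sized: the article gives neither the share of women below 23 cm nor the relation of MUAC to any biomarker.
- *That antimicrobials in EIMP alter the stool bacterial results.* The article lists no array targets and names no antibiotic, and the comparator arm also received infection treatment under syndromic care.

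**Conclusion.** The point holds as one of attribution. It is clear for the iodised-salt aim and weaker for deworming, where the sentence is looser. By design structure alone, neither effect can be isolated; this needs no numerical assumption. The 28% to 38% figure comes straight from Table 1 and assumes the full daily serving is eaten.

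For BEP and adherence/dose the conclusion is conditional. These analyses are not protected by randomisation, and a comparison by receipt would be confounded by undernutrition and would condition on a post-randomisation variable. The size of that confounding is unknown. The matter should be settled before component results are reported.

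**What to change.** - Reword the iodised-salt and deworming aims as effects of ENP and of EIMP.
- For BEP, compare ENP with not-ENP by assignment among women with enrolment MUAC below 23 cm in both arms, with an ENP × enrolment-MUAC interaction. This assumes that enrolment MUAC was recorded in both arms. Women who qualified later stay in their enrolment stratum.
- Report the low-MUAC contrast as the effect of the package including BEP. State that the interaction isolates BEP only if the other ENP components act equally in both strata.
- For iodine and thyroid outcomes, also report ENP v not-ENP in the stratum at or above 23 cm at enrolment, noting that the supply rule lets some of these women receive BEP later. This is the closest available contrast with little BEP, and it is still salt plus counselling plus IFA support.
- Label adherence and dose analyses as observational and adjust them for enrolment MUAC.

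The cost is wording, one prespecified baseline subgroup, and narrower claims. Stratum estimates will be less precise: the substudy has three enhanced-nutrition and three routine-care health centres, so each stratum's ENP contrast rests on three centres against three.

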##### Iron status

We will analyse maternal serum for hepcidin, ferritin and soluble transferrin receptors to assess iron status. Total body iron will be calculated, and adjustments will be made for inflammation biomarkers (CRP and AGP) as recommended by the BRINDA project.^23^ The impact of the ENAT intervention on iron status will be evaluated, and associations between maternal prenatal iron status and child development outcomes will be examined. Finally, we will preserve blood samples for further testing of other micronutrients, such as selenium.^24^

### Metabolomics

Metabolomics is the systematic analysis of human biofluids, such as blood, to describe the composition and metabolic changes within the human body at a specific time point. It is essential to understand the biological processes and pathways influenced by interventions involving biological elements like supplements and antibiotics. Using maternal and infant whole blood samples collected across multiple time points via VAMS and DBS, we will conduct untargeted metabolomics analysis using rapid liquid chromatography-mass spectroscopy (rLC-MS) at Sapient Analytics (California, USA).^25^ Internal control samples will be used to standardise testing and counteract potential batch effects. This discovery work will help us to identify metabolites both in pregnant women and infants that are associated with the ENAT interventions, as well as adverse birth outcomes such as preterm birth, small-for-gestational-age birth and LBW.

### Microbiome profiling

Multiple studies have established the importance of the maternal microbiome on infant birth and growth outcomes; however, there is limited data on the effects of intervention during pregnancy.^26^ Using stool samples collected via OMNIgene.GUT collection kits, we will profile the maternal and infant gut microbiomes through shotgun metagenomic sequencing at the University of Wisconsin (Madison, WI, USA). This approach will accurately measure the richness and abundance of microbes and the differences between those receiving the ENAT nutrition intervention, infection intervention, both or neither. Additionally, we will also investigate how the maternal microbiome during pregnancy may impact infant birth and neurodevelopmental outcomes. This analysis will be conducted in collaboration with the [name] Laboratory at Stanford University (Stanford, CA, USA).

### Gut enteropathogens

It has been hypothesised that enteropathogen infection may cause intestinal inflammation and contribute to stunting and micronutrient deficiencies in infants.^13^ Stool samples collected in DNA/RNA shield will be sent to the University of Virginia for testing using custom-designed TaqMan array cards (TAC). We will determine the pathogenic burden within pregnant women. We will also examine the impact of the ENAT deworming interventions on stool pathogens.

### Telomeres

Leucocyte telomere length will be determined from maternal and cord blood DBS DNA. DNA will be extracted from the samples using the Qiagen Qiamp Blood Mini Kit protocol at the [name] Laboratory at Boston Children’s Hospital (Boston, MA, USA). Telomere length will be assayed following a standardised protocol.^27^

### Statistical analyses

We will have two different approaches to our analyses. In the primary analysis, we will determine differences in biomarkers/profiles between the randomised study intervention arms, and in the secondary analysis, we will determine the associations of biomarkers with adverse outcomes (pregnancy or child developmental outcomes).

#### Intervention effects

In our primary analysis, we will examine differences in biomarkers or ’omics profiles across the randomised intervention study arms. We will use intention-to-treat as the primary analyses where individuals are analysed according to their originally assigned study arm, and in secondary analysis, we will also explore effects of individual interventions (ie, BEP) and adherence/dose. Outcomes will be compared between the primary factors (ENP or EIMP) to determine their marginal effects (ENP vs not-ENP, and EIMP vs not-EIMP). We will estimate differences in biomarkers, using linear mixed regression models. Potential confounding bias should be minimised due to the randomised study design; however, we will assess group differences in demographic and clinical characteristics at both cluster- and individual randomisation levels, as recommended by Consolidated Standards of Reporting Trials.^28^ Baseline covariate imbalances associated with both the outcome and exposure status (p<0.10) will be included in adjusted models as potential confounders. Multiple births will be excluded from analyses using birth outcomes due to the known increased rate of preterm birth and growth restriction among multiple deliveries. When large volumes of tests are conducted for metabolomics or genomics analyses, we will use the Benjamini-Hochberg method to correct for multiple testing, as appropriate.

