**Methods and analysis:**

The Enhancing Nutrition and Antenatal Infection Treatment (ENAT) study was a 2×2 factorial, randomised clinical effectiveness study conducted in Amhara, Ethiopia from August 2020 to June 2022. We cluster-randomised pregnant women (n=2399) to receive either a nutrition intervention (iron-folic acid (IFA), iodised salt and balanced energy-protein supplementation for women with mid-upper arm circumference <23 cm) or routine care (IFA only), and individually randomised women to an infection control intervention (genitourinary tract infection screening-treatment and screening-treatment of stool parasites) or routine care (syndromic approach). Participants were followed until 1 month postpartum. A subset of 532 women-infant dyads were consecutively enrolled in the biospecimen substudy from July 2021 to August 2022. Specimens were collected at enrolment (<24 weeks) and antenatal care follow-up (third trimester), and 1–6 months postdelivery. A subset of ENAT mother–infant dyads (n=462) was enrolled in the Longitudinal Infant Development and Growth study that followed infants until 24 months postpartum, from February 2023 to June 2024. We will determine the impact of ENAT interventions on micronutrient status, inflammation biomarkers and metabolomic and microbiome profiles. We will also determine the association of these profiles with birth outcomes and infant neurodevelopment.

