## Methods

### Study setting and population

The ENAT study was conducted in 12 health centres in Amhara, Ethiopia. For ENAT, pregnant women at ≤24 weeks gestation presenting for antenatal care at the study sites were enrolled in the study if they met the eligibility criteria. Women were excluded if they had a non-viable pregnancy at ≤24 weeks gestation, determined by a lack of heartbeat on the enrolment ultrasound or were unable to return for follow-up visits (typically >2 hours travel distance from health centre). Within the ENAT study, the biospecimen substudy was conducted in a subset of six health centres (three enhanced nutrition and three routine care centres) that had functional laboratory rooms and were accessible from the regional city/central laboratory (Ambesamie, Arbgebeya, Lalibela, Legdiya, Yifag and Yismala). The LIDG study enrolled the infants born to women included in these ENAT biospecimen health centres who intended to stay in the study catchment area after giving birth. Children with major congenital anomalies, severe morbidity or developmental disorders, acute symptoms of illness (eg, headache, vomiting or dizziness) or neonatal encephalopathy were excluded from the study.

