### Biospecimen collection and processing

Maternal whole blood, serum, stool, urine, vaginal swabs and breastmilk samples were collected at trimesters 1, 2 and 3, and 1–3 months postdelivery. Umbilical cord whole blood and serum, and infant whole blood and stool were also collected at birth and 1–2 months postnatal visit(s), respectively. For samples collected during the COVID-19 pandemic, all local health and prevention protocols and guidance were followed to collect and process biospecimens. Specimens were collected at each study health centre by trained laboratory technicians assisted by study nurses and transported using triple packaging containing ice packs within 48 hours of collection to the Amhara Public Health Institute (APHI) central laboratory for processing and longer storage at −80°C. A comprehensive list and timing of biospecimens collected in this study are shown in table 2.

**Table 2 T2:** ENAT study visits and biospecimen collection

Biospecimen type (collection mechanisms)	Enrolment visit (<24 week)	ANC follow-up visit (~30–34 weeks)	Birth (within 72 hours of birth)	Postnatal follow-up visit (1–6 months)*
Urine	M	M		
Vaginal swab	M	M		
Serum	M	M	C	
Whole blood (DBS)	M	M	C	I
Whole blood (VAMS)	M	M	C	I
Stool (Genotek)	M	M		M, I
Stool (TaqMan)	M	M		M, I
Breastmilk				M

* Postnatal visits were stopped prematurely due to conflict in the study region.

ANC, antenatal care; C, cord; DBS, dried blood spot; ENAT, Enhancing Nutrition and Antenatal Infection Treatment; I, infant; M, maternal; VAMS, volumetric absorptive microsampling.

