##### Dried blood spots (DBS)

Maternal prenatal DBS samples were collected from women while they were providing blood for routine laboratory testing (haemoglobin/HIV/syphilis) in trimester 1. Samples from trimesters 2 and 3 were collected via finger-stick. After the blood was collected into EDTA tubes, the tubes were gently inverted 8–10 times. Using a micropipette, 50–80 µL of blood was placed on a single spot on a Whatman 903 Proteinsaver Card (Cytiva, US), and this process was repeated three more times for a total of four spots. The Whatman cards were air-dried for 24 hours at the study health centre laboratory and placed in an individual zippered plastic bag with a humidity indicator and 2–3 small silica gels. At APHI, approximately 20 DBS samples were stored within a larger zippered bag with silica gel pillows, humidity indicators and stored at −80°C.

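### Prespecify the enrolment value of each maternal biomarker in the primary model instead of leaving it to a p<0.10 imbalance screen

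*Protocol article*

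**What the plan says.** The Intervention effects section of the protocol article gives the primary model in one sentence: "We will estimate differences in biomarkers, using linear mixed regression models". The same section fixes how covariates are chosen. Arms are checked for demographic and clinical differences. Baseline variables found imbalanced and related to both outcome and arm, at p<0.10, then go into adjusted models. No sentence says whether the enrolment value of the analysed biomarker is a covariate, a repeated outcome or neither.

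Paired specimens exist. The abstract says: "Specimens were collected at enrolment (<24 weeks) and antenatal care follow-up (third trimester), and 1–6 months postdelivery". Table 2 marks maternal urine, vaginal swab, serum, dried blood spot, VAMS and stool at the enrolment visit and again at antenatal follow-up around 30–34 weeks. Cord, infant and breastmilk samples have no enrolment entry.

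The design is "cluster-randomisation of an enhanced nutrition package (ENP) intervention and individual-level randomisation of an enhanced infection management package (EIMP) intervention". The substudy was run in "a subset of six health centres (three enhanced nutrition and three routine care centres"), and its size is given as follows: "A subset of 532 women-infant dyads were consecutively enrolled in the biospecimen substudy".

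**The concern.** A covariate rule driven by observed imbalance selects on the wrong property. In a randomised comparison, a baseline measurement is useful because it predicts the outcome. That usefulness is the same when the arms happen to be balanced. The enrolment value of the same analyte is likely to be among the strongest predictors available, yet under this rule it would enter only in the minority of cases where chance made it differ between arms, and then only in an adjusted model.

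What is at stake is precision, for both factors. For ENP it matters more because the contrast rests on three centres per arm, so chance differences between centres make up much of its error. Leaving the choice to the data also means that different biomarkers would be analysed with different covariate sets, decided after the results are seen.

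**Working it through.** The article states no standard deviation, intracluster correlation (ICC), baseline–follow-up correlation or power for the substudy, so there is no figure to reproduce. The ICC, the correlations, equal centre sizes, equal EIMP arms and complete pairs for all 532 dyads are assumptions. Effects are in SD units.

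**1. How often the screen would pick the enrolment biomarker.** Under randomisation, a valid test at p<0.10 finds an imbalance in 10% of cases. A simulation of six centre means (200,000 draws, m = 532/6 = 88.7 women per centre, centre-level t test on 4 df) gave about 10% at every ICC from 0.01 to 0.10. Only the imbalance half of the rule was simulated. Requiring an association with the outcome as well cannot raise the figure.

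| ICC | Baseline gap above 0.2 SD between ENP arms | Such a gap present and not selected |
|---|---|---|
| 0.01 | 9% | 4% |
| 0.02 | 16% | 9% |
| 0.05 | 32% | 23% |
| 0.10 | 46% | 36% |

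Both columns are shares of all allocations. A screen that ignored centre would select the biomarker in 23% to 60% of allocations.

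**2. EIMP (individual randomisation).** ANCOVA multiplies the variance by 1 − ρ². The difference detectable with 80% power at two-sided 5%, 266 v 266, is (1.960 + 0.842) × √(2/266) × √(1 − ρ²).

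| ρ (assumed) | Variance cut | Detectable difference | Equivalent dyads, 532/(1 − ρ²) |
|---|---|---|---|
| 0 | none | 0.243 SD | 532 |
| 0.3 | 9% | 0.232 SD | 585 |
| 0.5 | 25% | 0.210 SD | 709 |
| 0.7 | 49% | 0.173 SD | 1043 |

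**3. ENP (three v three centres).** Unadjusted, SE² = (2/3)[ICC + (1 − ICC)/m]. At ICC 0.05 the bracket is 0.0500 + 0.0107 = 0.0607, so 0.0500/0.0607 = 82% of the variance lies between centres. With a correlation of 0.5 at both levels, each term is multiplied by 0.75. On 4 df the detectable difference then falls as follows:

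- ICC 0.01: 0.447 to 0.387 SD
- ICC 0.02: 0.541 to 0.469 SD
- ICC 0.05: 0.757 to 0.655 SD
- ICC 0.10: 1.019 to 0.883 SD

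When the two correlations differ, the result depends on the slope. Write rc for the correlation of centre means and ri for the individual correlation. ANCOVA on individual values applies essentially the within-centre slope, so with equal variances at the two visits the centre term is multiplied by 1 + ri² − 2·ri·rc. A separate, optimal centre-level slope would give 1 − rc². At ICC 0.05:

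| rc, ri | Individual-level ANCOVA | Optimal centre slope |
|---|---|---|
| 0.6, 0.4 | (0.05×0.68 + 0.0107×0.84)/0.0607 = 0.71, a 29% cut | 0.675, a 32% cut |
| 0.8, 0.5 | (0.05×0.45 + 0.0107×0.75)/0.0607 = 0.50, a 50% cut | 0.429, a 57% cut |
| 0.2, 0.5 | centre multiplier 1.05; (0.0525 + 0.0080)/0.0607 = 0.997, no gain | not relevant here |

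The optimal column is optimistic: it requires a slope estimated from six centre means and uses up a degree of freedom.

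**4. Validity without adjustment.** In the same simulation, the unadjusted ENP test with centre handled at cluster level kept a type I error of 0.049 to 0.051.

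**The case against.** The strongest reply is that a condensed article need not list model terms. A mixed model could carry the enrolment value as a repeated measure, the Metabolomics section speaks of samples from several time points, and an enrolment biomarker could itself pass the screen. This stands against any claim that the plan never uses the enrolment value, which a reader might infer from the silence. It does not rescue the screen, which the article states outright.

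Three further readings are tempting and not supported.

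- A reader might infer that differences between the three ENP and three routine-care centres bias the ENP effect. Under cluster randomisation they are random error, and the simulation shows the test holding its level when centre is modelled. The centres were picked for laboratory function and access, and the trial was open-label. Those facts make an enrolment comparison worth having, but the article shows no imbalance. The three-v-three argument does not apply to EIMP.
- A reader might infer that an arm effect averaged over both visits would dilute the result, or that a change score is planned. The article proposes neither.
- A reader might hold the change of blood source against using the enrolment value, because for dried blood spots "Samples from trimesters 2 and 3 were collected via finger-stick" while trimester 1 used routine draws. A shift common to both arms does not distort the contrast, though mixed sources may lower the correlation. Serum was taken by venipuncture at each visit, and urine, swab and stool are unaffected.

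It is also fair to say that the change is not free. Table 3 does not state which visits will be assayed, and single-copy samples stay in Ethiopia, so pairs may be incomplete at the overseas laboratories.

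**Conclusion.** The point holds as a weakness of method, not as an error of validity. Applied as written, the p<0.10 screen would leave the enrolment biomarker out about nine times in ten when the test is valid, although paired maternal specimens were collected.

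For EIMP the forgone gain is a variance reduction of 9%, 25% or 49% at assumed correlations of 0.3, 0.5 or 0.7. For ENP at an assumed ICC of 0.05, individual-level adjustment gives about 29% to 50% when centre means track well (0.6 to 0.8), and essentially nothing when they track weakly (0.2). Adjustment leaves the number of clusters at six.

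These sizes rest on the assumed ICC and correlations, equal centres and complete pairs. They apply only to maternal biomarkers measured at enrolment. The article does not state outright that the enrolment specimen precedes the first supply of the interventions, and the argument needs that.

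**What to change.** For maternal biomarkers assayed at enrolment, replace the screen with a prespecified term:

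- Put the enrolment value of the same analyte in the primary model regardless of imbalance. Use ANCOVA with the later value as outcome, or a constrained longitudinal model with a common baseline mean and an arm-by-visit term.
- Include centre as a random effect. For ENP, consider separate centre-mean and individual-level baseline terms only if six centres allow it.
- Do not extend the rule to cord, infant or breastmilk outcomes.
- State how incomplete pairs are handled; the constrained longitudinal model retains women with one of the two values.
- Confirm that enrolment specimens were taken before any intervention was supplied.

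No new collection is needed. The cost is wording in the analysis plan where enrolment specimens are already to be assayed, and additional assays where they are not.
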